### Participant timeline {13}

The study schedule is shown in Fig. 2.

**Fig. 2 Fig2:**
[figure not shown]
Study schedule

### Sample size {14}

The intervention group is the continuous ambulatory glucose monitoring group (CG group), and the control group is the conventional arterial blood glucose monitoring group (C group). According to the previous literatures and our pre-experiment results, the intraoperative CV % in the liver transplant control group is about 40%, and it is expected that the intraoperative CV % in the intervention group could be reduced by 20%. Thus, we set bilateral α = 0.05 with 80% power, according to the sample size formula:$$\begin{array}{cc}N=\frac{{\left({Z}_{a}+{Z}_{B}\right)}^{2}\left(1+\frac{1}{k}\right)P(1-P)}{{(Pe-{P}_{c})}^{2}}& p=\frac{Pe+kPc}{1+k}\end{array}$$

We estimate that the sample size for each group should be 78 cases. We set the sample size for each group to 90 to allow for up to 10% dropouts.

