### Outcomes {12}

#### Primary outcomes

Intraoperative glucose coefficient of variation. In this study, the intraoperative coefficient of variation of blood glucose will be extracted from the CGM data for each participant (from the beginning of skin incision to the end of suture).

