### Assignment of interventions: allocation

#### Sequence generation {16a}

An investigator ([name]) who will not be involved in the patient recruitment and treatment process uses SAS 9.2 software (SAS Institute Inc., Cary, NC, USA) to generate a 0 s and 1 s random sequence (1:1), corresponding to sequence numbers from 1 to 180 for each sequence.

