### Statistical methods

#### Statistical methods for primary and secondary outcomes {20a}

Continuous variables such as CV%, mean blood glucose, and liver transaminases levels and other indicators will be tested for normality using Kolmogorov–Smirnov test. Measures satisfying normal distribution will be expressed as mean ± standard deviation, and median (interquartile range) when data are not normally distributed. Qualitative data such as the incidence of hypo/hypoglycemia, SSIs, and MACE will be expressed as frequencies (percentages).

Normally distributed data will be compared between two groups using *t*-test, multiple groups will be compared using ANOVA, and non-normally distributed data will be compared using Mann–Whitney *U*-test. The chi-square test will be used for comparison between groups for numerical data. Comparisons of CV%, the primary outcome, will be made using either the *t*-test or the Mann–Whitney *U* test.

Repeated measures will be compared using analysis of variance (ANOVA). Blood glucose analysis will be performed using multifactorial analysis.

In this study, the accuracy of CGM monitoring will be tested simultaneously for patients in the CG group. Pearson linear correlation analysis will be applied to determine the correlation between CGM- and ABG-derived glucose levels; Clarke error grid analysis will be used to evaluate the consistency between CGM- and ABG-derived glucose levels. The formula: [ABG glucose − CGM glucose)/ABG glucose] × 100% will be applied to calculate the overall clinical mean relative error. If this error value is ≤ 17% and the sum of the data falling in areas A and B in the Clark error grid analysis is not less than 95% of the total, the accuracy will be judged to be satisfactory.

All analyses will be performed using SPSS 26.0 (SPSS, USA) and STATA 14.0 (StataCorp LP, College Station, TX).

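### The sample size treats a continuous primary outcome (CV%) as an event proportion, so the stated 80% power is not established for the planned test

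*Protocol article*

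**What the plan says.** All references are to the protocol article.

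- **Outcome.** Under Primary outcomes, "the intraoperative coefficient of variation of blood glucose will be extracted from the CGM data for each participant", over the period from skin incision to the end of suturing. Each patient contributes one continuous value.
- **Test.** Under Statistical methods {20a}: "Comparisons of CV%, the primary outcome, will be made using either the" t-test or the Mann–Whitney U test.
- **Planning values.** Sample size {14} cites earlier literature and the centre's own pre-experiment results. It says that "the intraoperative CV % in the liver transplant control group is about 40"%, and that "it is expected that the intraoperative CV % in the intervention group could be reduced by 20"%. It does not say whether the 20% is absolute or relative, and it gives no SD.
- **Error rates.** "we set bilateral α = 0.05 with 80% power".
- **Formula.** The section prints N = (Zα + Zβ)² (1 + 1/k) P(1−P) / (Pe − Pc)², with P = (Pe + kPc)/(1 + k).
- **Result.** "We estimate that the sample size for each group should be 78 cases. We set the sample size for each group to 90", the increase being an allowance for up to 10% dropout.
- **Allocation.** Sequence generation {16a} is 1:1, so k = 1.

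**The concern.** P(1−P) is the variance of a yes/no outcome. It is fixed by the event rate, so a two-proportion formula needs no separate SD. A coefficient of variation is written in percent but is not a proportion of patients. A mean CV of 40% says nothing about how far CV% differs from one patient to the next, and that spread determines the power of a t-test or rank test. The protocol names no binary CV endpoint as primary, so the formula has no outcome to which it applies.

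At stake is the only power justification for the primary outcome. If the final report repeats 78 per group and 80% power, it will attach those figures to a test they were not derived for. Nobody can tell from the document whether 180 patients are more than enough or too few.

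**Working it through.** **Step 1. Reproduce the plan's figure from its own formula.**

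Inputs: Pc = 0.40 and two-sided α = 0.05 with 80% power (Sample size {14}); k = 1 (Sequence generation {16a}). (Zα + Zβ)² = (1.960 + 0.842)² = 7.849.

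- *Absolute reading, 40 to 20:* Pe = 0.20, P = 0.30. N = 7.849 × 2 × 0.30 × 0.70 / 0.20² = 82.4, so 83 per group. This is not 78.
- *Same reading, unpooled variance (not the formula printed):* N = 7.849 × (0.40 × 0.60 + 0.20 × 0.80) / 0.20² = 7.849 × 0.40 / 0.04 = 78.49. Rounded up this is 79; rounded down it is 78.
- *Relative reading, 40 to 32:* Pe = 0.32. The printed formula gives 565.1, nowhere near 78. The figure serves only to show which reading was used. It is not a requirement for this trial, because the formula does not fit the endpoint.

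So 78 most likely came from the unpooled variant, rounded down, with CV% assumed to halve from 40 to 20.

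Dropout: 78/0.9 = 86.7, so 90 covers the stated 78. 90 × 0.9 = 81 evaluable per group.

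**Step 2. What the planned test needs.**

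For a two-sample comparison of means, n per group ≈ 2 (Zα + Zβ)² SD² / Δ², where Δ is the difference in CV points and SD is the between-patient SD of CV%. The protocol gives no SD, so no single corrected sample size exists.

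**Step 3. What 81 evaluable per arm deliver.**

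A two-sided t-test at 0.05 with 81 per arm has 80% power for a standardised difference of 0.443, that is 0.44 SD. The SDs below are assumptions, in CV points.

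| Target drop | Assumed SD | Power, 81 per arm |
|---|---|---|
| 20 points (40 to 20) | 30 | 98.8% |
| 20 points | 40 | 88.5% |
| 8 points (40 to 32) | 15 | 92% |
| 8 points | 20 | 72% |
| 8 points | 25 | 53% |

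The SD at which power falls to 80% is Δ/0.443: about 45 points for a 20-point drop (20/0.443 = 45.1) and about 18 points for an 8-point drop (8/0.443 = 18.1).

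**The case against.** The strongest reply is that the trial may be amply powered anyway. On the reading evidently used, a 20-point drop, 81 per arm keep at least 80% power unless the SD exceeds about 45 points, which is more than the assumed control mean of 40. That stands, and it rules out one tempting inference. A reader might conclude from the wrong formula that the trial is underpowered. The document does not support that: without an SD, and without knowing whether 20 or 8 points is meant, power may be above or below 80%.

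A second reply concerns 78 against 83. A standard variant of the formula gives 78.49, so the figure is explicable, and the trial randomises 90 per arm in any case. This also stands. The discrepancy shows that the printed formula is not the one used, but it is a minor point. Nor should figures such as 83 or 565 be read as the number of patients this trial lacks, because they come from a formula for a different kind of endpoint.

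A third inference to resist is that a null result would be uninterpretable. It would still be read from the estimated difference and its confidence interval, which use the observed spread. The planning error does not bias the comparison. What is lost is the advance justification of 80% power.

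None of this rescues the section as written. A sample size that happens to suffice does not make its stated justification correct.

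**Conclusion.** Wrong as written. The sample size calculation does not match the continuous primary outcome or the planned test, and the SD that governs power is absent. The stated 80% power is therefore not established, in either direction.

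What holds without an assumed SD is that 81 evaluable per arm give 80% power for 0.44 SD by a two-sided t-test. Everything in CV points rests on SDs assumed here. Within the ranges shown, power runs from 53% (8-point drop, SD 25) to 98.8% (20-point drop, SD 30). The figures are for the t-test; if the Mann–Whitney U test is used, they are approximate.

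Two lesser errors sit in the same section. The printed formula gives 83 per group rather than 78, and the 20% reduction is not identified as absolute or relative, although only the absolute reading comes near 78.

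**What to change.** Rewrite the sample size section as follows:

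1. Replace the two-proportion formula with a two-sample calculation for means, or for a rank test if that is the intended primary test.
2. State the target difference in CV points, and say whether 20% means 40 to 20 or 40 to 32.
3. State the between-patient SD of intraoperative CV% and its source: the pre-experiment results if they provide one, otherwise the literature. If neither does, show a range.
4. Delete 78.
5. Report the power, or the detectable difference in CV points, that 90 randomised (81 evaluable) per arm deliver, even if the power is below 80%.

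The cost is one calculation and a reworded section. Whether 90 per arm is enough for the chosen target cannot be settled until the SD is known, so the recalculation should not presume that it is.

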#### Criteria for removal from the trial

Failure to manage anesthesia or blood glucose in accordance with the study protocolIntraoperative massive blood loss, defined as blood loss exceeding 50% of systemic blood volume within 3 h or blood loss at a rate of > 150 ml/hDeath within 3 months after LTLoss of follow-upVoluntary patient withdrawal from the studyFailure to record study data

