#### Methods in analysis to handle protocol non-adherence and any statistical methods to handle missing data {20c}

All randomized participants will be included in the main analyses. An intention-to-treat analysis will be carried out relating to any protocol non-adherence or dropouts. Per-protocol dataset will also be performed for any of the missing data. Besides, we anticipate little loss to follow-up for the primary outcome. Nevertheless, if there is more than 5% missing data for the primary outcome, we will perform a sensitivity analysis using multiple imputations for the missing data.

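### The blood-loss removal rule has two limits about four to six times apart, and the protocol does not settle whether patients removed under it stay in the primary analysis

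*Protocol article*

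**What the plan says.** **Sample size {14}.** "We estimate that the sample size for each group should be 78 cases". The next sentence reads "We set the sample size for each group to 90 to allow for up to 10% dropouts". The section does not say which kinds of loss the 10% covers and does not refer to the removal criteria.

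**Criteria for removal from the trial.** One criterion is massive intraoperative blood loss. It is met by "blood loss exceeding 50% of systemic blood volume within 3 h" or, alternatively, by a rate above 150 ml/h. The other criteria are management off protocol, death within 3 months, loss to follow-up, withdrawal and unrecorded data.

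**Primary outcomes, under {12}.** The glucose coefficient of variation (CV%) is taken from the CGM record between incision and closure. Under {11a}, CGM is recorded in both groups.

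**Section {20c}.** "All randomized participants will be included in the main analyses". Intention-to-treat is named for non-adherence and dropouts, and a per-protocol dataset is added.

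**Section {18b}.** Complete-case analysis is planned for all outcomes.

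**Sections {16b} and {17a}.** Care providers and study staff know the allocation. Follow-up staff, outcome assessors and data analysts do not.

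**The concern.** There are two linked problems.

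First, the two limits are offered as alternative definitions of one event, but they describe very different amounts of bleeding. As they are joined by *or*, the lower one decides who is removed.

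Second, the trigger is a post-randomisation event inside the window in which the primary outcome is measured. The protocol does not say who applies the rule, but the staff who would see the bleeding know the allocation. The Background section names fluid infusion and traumatic stimuli among the causes of intraoperative glucose change, so patients who bleed more could plausibly have a higher CV%. Dropping them would then select on something related to the outcome, and the comparison would no longer be of the groups as randomised. Enrolling more patients would not cure that.

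The protocol contains a statement that would prevent this, in {20c}, and one that points the other way, in the removal criteria. It does not say which prevails.

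**Working it through.** **1. Reproduce the plan's 78.** Inputs from {14} and {16a}:
- "we set bilateral α = 0.05 with 80% power", so z values of 1.96 and 0.84, and (1.96 + 0.84)² = 7.84.
- "the intraoperative CV % in the liver transplant control group is about 40" per cent, entered as Pc = 0.40.
- "it is expected that the intraoperative CV % in the intervention group could be reduced by 20" per cent. Only an absolute drop, Pe = 0.20, gives a size near 78; a relative cut to 0.32 gives about 561 to 565.
- Allocation 1:1, so k = 1.

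With unpooled variance: 7.84 × (0.20 × 0.80 + 0.40 × 0.60) / 0.20² = 7.84 × 0.40 / 0.04 = 78.4, which matches the stated 78. The printed formula pools the variance and gives 7.84 × 2 × 0.30 × 0.70 / 0.04 = 82.3. That is a separate matter; the stated 78 is used below.

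**2. The allowance.** 78 / (1 − 0.10) = 86.7, so 87 per group are needed. The plan sets 90, and 90 × 0.90 = 81, which is above 78. The largest loss that still leaves 78 is 90 − 78 = 12, and 12 / 90 = 13.3%.

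**3. The two blood-loss limits on one scale.** Assumption (not in the protocol): blood volume 70 ml/kg, weight 50 to 80 kg.

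| | 50 kg | 80 kg |
|---|---|---|
| Blood volume | 3,500 ml | 5,600 ml |
| Half of it over 3 h | 1,750 / 3 = 583 ml/h | 2,800 / 3 = 933 ml/h |
| Ratio to 150 ml/h | 3.9 | 6.2 |
| 150 ml/h for 3 h (450 ml) as share of blood volume | 12.9% | 8.0% |

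With 65 to 75 ml/kg over the same weights, the ratio runs from 3.6 to 6.7. The limits would coincide only if 450 ml were half the blood volume, that is, at a blood volume of 900 ml. For any adult, then, bleeding that meets the 50% limit also exceeds 150 ml/h on average over that period, and the 50% limit adds nothing.

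**4. What happens to a removed patient.**
- *If {20c} governs:* the patient stays in the main analysis, and blood loss costs it nobody.
- *If {18b} is applied alone:* the primary outcome is complete at the end of surgery, so a bleeding patient with a full CGM trace is a complete case and also stays.
- *If the removal criteria govern:* the patient leaves. All the removal reasons then draw on the same 12 places per group, including death within 3 months, which occurs after the primary outcome has been measured.

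**5. Size under the third reading.** Any total removal share above 13.3% leaves fewer than 78. For illustration only, assumed shares of 20% and 30% would leave 90 × 0.80 = 72 and 90 × 0.70 = 63.

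**The case against.** The strongest reply is that {20c} already settles the matter: every randomised participant is in the main analyses, and the per-protocol dataset is the natural place for the removal criteria. On that reading nothing is lost from the primary comparison, and the recommended handling is what the protocol already intends. This is a fair reading and may well be what was meant. But the criteria are headed as removal from the trial, not from a per-protocol set, and no sentence links the two. The conflict therefore stands, although its consequence is conditional.

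A second reply is that 150 ml/h may be a slip in the figure or its time unit, since it sits beside half the blood volume under the label massive. That is possible. It supports checking the rate, but as printed the rule would operate at 150 ml/h.

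Three stronger conclusions are tempting and should not be drawn.
- *That the 10% allowance is miscalculated.* It is not: 87 are needed for 78 plus 10%, and 90 are planned.
- *That the trial will lose far more patients than it can spare, and its power with them.* The protocol gives no distribution of blood loss and no operating time, so the removal share is unknown. Nor can a loss of power for CV% be derived, because 78 comes from a two-proportion formula with no standard deviation and so implies no standardised effect on a continuous outcome.
- *That blood loss will not be recorded because it is absent from the data list in {18a}.* That list is condensed in a journal article, and the schedule figure is not available here.

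Different application of the rule in the two groups is likewise a possibility that the design leaves open, not something the protocol shows.

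**Conclusion.** The point holds as an internal contradiction with a conditional consequence. The two limits differ by a factor of about 3.9 to 6.2, given 70 ml/kg and 50 to 80 kg. That the lower one decides every case does not depend on those assumptions for any adult. The removal criteria and {20c} disagree on whether these patients count in the primary analysis.

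If removal prevails, the primary comparison excludes patients on a post-randomisation event that may be related to the outcome, and the 78 per group is missed once total removals exceed 12 of 90. If {20c} prevails, neither harm occurs. The possible link between bleeding and CV% is an inference from the Background section, not a documented figure. The matter deserves a clear correction because it bears on who is in the primary analysis, but the protocol does not show that the trial is underpowered.

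**What to change.** 1. Reconcile the two limits in the blood-loss definition so that they describe one event, checking the rate and its time unit. This review takes no position on which limit is right.
2. State, in the removal criteria and in {20c}, that massive blood loss does not remove a randomised patient with a CGM trace from the primary analysis. Exclude such patients only in a per-protocol or sensitivity analysis.
3. State in {14} that the 10% allowance covers only patients without primary-outcome data. With that reading, 90 per group is consistent with the stated 78 and need not change for this reason.

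The cost is a few sentences of protocol wording. The small statistical price is some added variance in the primary comparison from patients who bleed heavily.

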### Recruitment {15}

All patients proposed for orthotopic liver transplantation are screened for inclusion and exclusion criteria one day prior to surgery.

### Assignment of interventions: allocation

#### Sequence generation {16a}

An investigator ([name]) who will not be involved in the patient recruitment and treatment process uses SAS 9.2 software (SAS Institute Inc., Cary, NC, USA) to generate a 0 s and 1 s random sequence (1:1), corresponding to sequence numbers from 1 to 180 for each sequence.

#### Concealment mechanism {16b}

Random numbers, serial numbers, and group numbers will be placed in opaque sealed envelopes. Each sealed envelope will be sequentially numbered and kept in a secure location until the study is completed. After participants have signed informed consent and passed the inclusion and exclusion criteria screening, the same investigator ([name]) will open the envelopes with the same serial number in order of enrollment and inform the anesthesiologist of the treatment assignment. Participants and study stuff will not be blinded to the treatment assignment. Only follow-up stuff will be masked to treatment assignment.

#### Implementation {16c}

The study draws up the 0 s random sequence as the CG group and the 1 s random sequence as the C group. The assignment results will be stored in an electronic system until the study ended.

### Assignment of interventions: blinding

#### Who will be blinded {17a}

Only judicial assessors of outcomes and data analysts will be blinded to the group assignment, whereas care providers and patients are not blinded.

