### Intervention description {11a}

#### Blood glucose management

Blood glucose monitoring

Intraoperative glucose monitoring is performed in both groups using CGM (Guardian RealTime, Medtronic, USA) in combination with arterial blood gas. A disposable glucose monitoring probe will be placed in the patient's upper arm by the investigator 6 h before surgery and connected to the monitoring system.

In the CG group, intraoperative ABG testing will be performed if the CGM value is < 6.1 mmol/L or > 10.0 mmol/L, or the rate of change of CGM value > 1.67 mmol/(L·min). Blood glucose adjustment will be performed according to the arterial blood glucose value.

In the G group, CGM monitoring results were blinded to patients and investigators. Intraoperative arterial blood gas checks will be performed every 2 h, and blood glucose adjustments will be made based on blood glucose results, and the frequency of blood gas tests will be adjusted as needed. CGM is used to record intraoperative glucose data only.2)Blood glucose management target: The intraoperative blood glucose management target is 7.8 ~ 10 mmol/L in both groups.3)Blood glucose-lowering measures: see Table 1 for the intraoperative glucose management measures for patients in both groups.

**Table 1 Tab1:** Blood glucose intervention

Perioperative target blood glucose: 7.8 ~ 10 mmol/L • If ABG-derived blood glucose > 10 mmol/L measured for the first time, start insulin infusion Insulin dose and mode of administration: • Loading dose: 0.1 U/kg, I.V Maintenance dose: (blood glucose value/5)U/h, infusion			
**Blood glucose (mmol/L)**	**If BG increased from previous measurement**	**BG decreased from prior measurement by ≤ 1.67 mmol/L**	**BG decreased from prior measurement by > 1.67 mmol/L**
**> 13.4**	Increase rate by 3U/h	Increase rate by 3U/h	No change in rate
**11.7 ~ 13.4**	Increase rate by 2U/h	Increase rate by 2U/h	No change in rate
**10.0 ~ 11.7**	Increase rate by 1U/h	Increase rate by 1U/h	No change in rate
**7.8 ~ 10.0**	No change in rate	No change in rate	No change in rate
**6.1 ~ 7.8**	No change in rate	Decrease rate by 50%	Hold insulin infusion
**5.5 ~ 6.1**	• Hold insulin infusion • Check BG every 2 h • Restart infusion if BG > 10 mmol/L		
**3.9 ~ 5.5**	• Hold insulin infusion • Check BG every 30 min until BG > 5.5 mmol/L, resume BG checks every 2 h • Restart infusion at 1/2 the prior infusion rate if BG > 10 mmol/L		

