#### Anesthesia management

Preoperative: Informed consent will be signed preoperatively. Potential participants will be identified by reviewing the inpatient list or surgery schedule, and patients will be visited to sign the informed consent and baseline information will be collected. For patients included in CG group, a disposable glucose monitoring probe is placed and connected to the monitoring system 6 h prior to surgery.Intraoperative: reliable intravenous access will be established after the patient enters the operating room, and electrocardiograph, blood pressure, pulse oximetry, end-expiratory carbon dioxide, and bispectral index (BIS) monitoring will be routinely performed. After adequate preoxygenation, standardized induction of anesthesia is started with propofol or etomidate, sufentanil or fentanyl, rocuronium bromide, or *cis*-atracurium. The actual drug dose should be adjusted by a qualified anesthesiologist based on the patient’s circulatory changes and surgical tolerance. Intraoperative anesthesia is maintained using total intravenous anesthesia, inhalation anesthesia, or a combination of static and inhalation anesthesia to maintain a stable depth of anesthesia. All medications should be recorded in detail and the patient should be transferred to the ward or recovery room or intensive care unit (ICU) for observation after the surgery.Postoperative analgesia: After the surgery, patients routinely use a patient-controlled analgesic device with a recommended analgesic formulation of sufentanil 250 μg + ondansetron 20 mg + saline to 250 ml, with specific parameters of the analgesic pump adjusted according to the patient’s condition. With the regular postoperative analgesic dose, if the patient still has moderate or above postoperative pain (defined as: numerical rating scale ≥ 4/10), additional analgesic drugs can be added with the permission of the physician in charge, but the reason for administration and the type of drug administered should be recorded in detail.

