##### Follow-up period

Patients were followed up on postoperative days 1 to 7 and days 15, 30, 60, and 90. Follow-up will be conducted by the investigator in the ICU or general ward during hospitalization and by telephone after discharge, respectively. The following information will be collected during the follow-up period:Incidence of SSIsIncidence of other infections: abdominal, pulmonary, and urinary tract infectionsPostoperative liver function: liver function and coagulation tests on postoperative days 1–7Incidence of MACE: cardiovascular death, myocardial infarction, and strokeLength of postoperative ICU stay and hospitalizationAll-cause mortality within 30 daysRe-hospitalization rate within 90 daysSecondary transplantation rate within 90 days

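### Patients are left unmasked without need, exposing mainly telephone-collected infections up to day 90, and the masking sections disagree on who is masked

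*Protocol article*

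**What the plan says.** Two sections of the protocol article decide that patients know their arm. Concealment mechanism {16b} states: "Participants and study stuff will not be blinded to the treatment assignment". Who will be blinded {17a} states: "Only judicial assessors of outcomes and data analysts will be blinded to the group assignment, whereas care providers and patients are not blinded".

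The same two sections name who is masked, and differ. {16b} adds: "Only follow-up stuff will be masked to treatment assignment". {17a} limits masking to outcome assessors and data analysts.

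The Follow-up period section under {18a} schedules contacts on days 1 to 7 and on days 15, 30, 60 and 90. It says who makes them: "Follow-up will be conducted by the investigator in the ICU or general ward during hospitalization and by telephone after discharge, respectively".

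On the sensor, Blood glucose management under {11a} states: "Intraoperative glucose monitoring is performed in both groups using CGM (Guardian RealTime, Medtronic, USA) in combination with arterial blood gas". Primary outcomes under {12} states that "the intraoperative coefficient of variation of blood glucose will be extracted from the CGM data for each participant". Anesthesia management, however, says: "For patients included in CG group, a disposable glucose monitoring probe is placed and connected to the monitoring system 6 h prior to surgery". Study setting {9} describes the control group as monitored by ABG alone.

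**The concern.** The trial asks whether CGM-guided management improves prognosis, and Secondary outcomes {12} compares infections, liver function and MACE between arms at 3 months. After discharge the only source of information the article describes is a telephone call. A patient who knows the arm can influence that call in two ways: by reporting symptoms more or less readily because of the arm, or by telling the caller which arm it was. A masked caller can correct neither.

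Such exposure is often unavoidable in a trial of a monitoring strategy. Here it appears avoidable, because the patient is anaesthetised while the arms are treated differently. The article gives no reason why the patient must be told. What is at stake is the credibility of part of the secondary, prognostic comparison.

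**Working it through.** No figure in the protocol belongs to this point, so the check sets the sections side by side.

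**1. When the arms differ.** Under {11a}, the CG arm has an intraoperative ABG test when a CGM value or its rate of change crosses a limit; the G arm has one every 2 h, adjusted as needed. Under {11c}, the alarm is on in the intervention arm during the transplantation. Both differences fall within the operation, and Anesthesia management describes induction and maintenance of anaesthesia for it. Under {16b}, the anesthesiologist is the person told the allocation. No step requires the patient to know it.

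**2. Whether wearing the sensor reveals the arm.** The abstract's Methods paragraph and {11a} put CGM on both groups, and {12} takes the primary outcome from CGM data in every participant. Study setting {9} (controls by ABG alone) and Anesthesia management (probe placement mentioned for CG only) point the other way. If only CG patients wore a probe, its presence would reveal the arm, and the primary outcome could not be measured in controls. Only the both-arms reading is compatible with the primary outcome, but the text must be reconciled before masking can work.

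**3. Whether withholding the allocation is enough.** The probe is placed and connected 6 h before surgery, when the patient is awake. {11a} hides CGM results from patients and investigators in the G group only. A CG patient who can see readings, next to a G patient who cannot, could work out the arm. The readings would therefore have to be kept from patients in both arms.

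**4. Which outcomes are exposed.**
- Primary CV%: recorded by the device from incision to end of suture. Not exposed.
- Liver function and coagulation on days 1 to 7, ICU and hospital stay, mortality, re-transplantation: measured, or matters of record. Not materially exposed.
- Myocardial infarction, stroke and re-hospitalisation: discrete events, with little room for the patient's opinion.
- SSI and other infections before discharge: collected in person in the ICU or ward.
- SSI and other infections after discharge, up to day 90: collected by telephone. Exposed.

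**5. Whether the person collecting outcomes is masked.** {16b} and {17a} each restrict masking to one set of roles, and the sets differ; read literally, both cannot be true. The Follow-up period section gives the task to the investigator without saying whether that person belongs to the masked follow-up staff or to the unmasked study staff of {16b}.

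**6. Size.** With no true effect, the spurious difference in an infection rate would be p × (s_CG − s_G), where p is the true rate of infections that depend on patient report and s is the probability of reporting in each arm. The article gives neither p nor s, nor a discharge day from which to derive the share collected by telephone. The expression cannot be evaluated. The masking change itself alters neither sample size nor power.

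**The case against.** The strongest reply is that the trial openly declares itself unblinded in the Discussion, lists the lack of double-blinding as a limitation, and masks where it matters: follow-up staff {16b}, outcome assessors and analysts {17a}, and the two people entering data (Data management {19}). Masked assessment with unmasked patients is a legitimate design, and the primary outcome is out of the patient's reach. This stands as far as it goes, and it confines the point to a few secondary outcomes. It does not give a reason for telling patients. The safeguard in the limitations paragraph, a detailed monitoring protocol and trained investigators, is directed at extra ABG testing, not at what patients report.

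The reply may also say that the word investigator in the Follow-up period section need not mean an unmasked person, since {19} uses it for masked people. That is fair. The section is unclear rather than in flat contradiction with {16b}; the conflict between {16b} and {17a} remains.

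A third reply is that masking patients is not free, because of the CG-only wording on the probe and the display hidden in G only. This is correct, and the change must cover both.

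Two stronger readings are tempting:
- A reader might infer that most of the event window rests on patient report, since (90 − 7)/90 = 83/90 = 92% of days lie outside the daily visits. That is a share of calendar days, not of events or telephone contacts. Follow-up is in person throughout the hospital stay, and no discharge day is given, so later scheduled contacts may still be on the ward.
- A reader might infer a false benefit of CGM of a few points. Assuming a true infection rate of 20%, reporting of 80% in CG and 90% in G gives 16% against 18%; 70% and 90% give 14% against 18%. Every input is invented, and the direction is too: closely monitored patients might report more, which would reverse the sign. The documents support no magnitude.

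**Conclusion.** The point holds in limited form. Patients are unmasked by stated choice although nothing in the design requires it, and this leaves mainly post-discharge SSI and other infections open to differential reporting, or to disclosure of the arm to the caller. The size and direction of any bias are unknown. Separately, the article contradicts itself on which roles alone are masked, and does not say that the person collecting day 1-90 outcomes is masked.

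The conclusion assumes that both arms wear the sensor, as the primary outcome demands, and that telephone calls after discharge are the main source for later infections, since no other is described. It would be wrong to read this as a threat to the CV% comparison or as evidence that the secondary results will be biased. It is an avoidable weakness that should be removed, not a flaw that invalidates the trial.

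**What to change.** - In {16b} and {17a}, use one identical list: patients, follow-up staff, outcome assessors and data analysts are masked; only the envelope holder and the intraoperative team know the arm. This narrows the unmasked care providers of {17a} to the intraoperative team.
- State that patients are not told their allocation, and that CGM readings are kept out of patients' view in both arms before and after surgery.
- Reconcile Study setting {9} and Anesthesia management with the abstract, {11a} and {12}, so that the probe is placed in both arms.
- In the Follow-up period section, name the masked follow-up staff as the collectors of day 1-90 outcomes.
- Section {17b} treats unblinding as not applicable; with patients masked, it needs a line on disclosure on request or for care.

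The cost is protocol wording, an instruction to staff and concealment of the display in the CG arm as already planned for G. Masked follow-up staff are already provided for in {16b}. Sample size, power and the primary analysis do not change. The downside is that an occasional patient may be unmasked on request or because care requires it; such cases can be recorded.
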